The sample will consist of 98 participants (49 in each intervention), who will be included according to the above criteria. The sample size calculation was performed considering a minimum difference of 4 mmHg, and dispersion (standard deviation) of ± 10 mmHg in systolic and diastolic BP. A statistical power of 80% and an alpha error of P<0.05 were adopted.

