## Statistical analysis

Shapiro-Wilk and Levene tests will be used for data normality and variance homogeneity, respectively. If the data present normal and homogeneous distribution, parametric statistics will be used. Transformations will be performed if the data do not present normal distribution to make them parametric. The Generalized Estimating Equations (GEE) and the Bonferroni post-hoc test will be used for the comparison between the moments and groups/ interventions. In addition, statistical analysis by protocol will be performed, in which those who have presented three consecutive absences in training will be excluded from the analysis, as well as those who obtain a frequency lower than 75% during the period of interventions. Statistical analysis by intention to treat will also be performed, in which all randomized participants will be included in the analyses. The level of significance adopted will be α = 0.05 for all analyses. The statistical package SPSS version 22.0 will be used to perform the statistical procedures.

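### The intention-to-treat comparison rests on a two-moment GEE that does not adjust for baseline blood pressure; a baseline-adjusted mixed model or ANCOVA would be more robust to drop-out and more precise at almost no cost

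*Protocol*

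**What the plan says.** The Statistical analysis section of the Protocol names one model: "The Generalized Estimating Equations (GEE) and the Bonferroni post-hoc test will be used for the comparison between the moments and groups/ interventions". It plans a per-protocol analysis that removes participants with poor attendance. For the other analysis, by intention to treat, it states that "all randomized participants will be included in the analyses". It gives no working correlation, weighting, imputation or missing-data assumption, and it does not claim validity under any particular drop-out mechanism.

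The Evaluations section sets two assessment times, before training (week 0) and after it (week 13). The Participants recruitment section plans the trial "considering a minimum difference of 4 mmHg, and dispersion (standard deviation) of ± 10 mmHg in systolic and diastolic BP", with 49 participants per arm. It mentions no drop-out rate and no allowance for drop-out.

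**The concern.** With two moments, a participant lost before week 13 is in the intention-to-treat set but has no outcome. What that participant contributes depends on how the GEE is fitted.

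Under an independence working correlation with a group-by-moment model, the week-0 mean comes from everyone randomised and the week-13 mean from completers only. If those who leave one arm had higher baseline pressure than those who stay, that arm's week-13 mean is too low and its reduction looks too large. When this differs between arms, it enters the TC4-TC2 contrast.

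The arms differ by design in weekly sessions, four against two, so a difference in who leaves is possible. The per-protocol analysis is no safeguard, because it selects on attendance.

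Apart from drop-out, a change contrast uses baseline less efficiently than adjustment for it does.

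**Working it through.** **The plan's own figure.** On this point the Protocol gives only a yardstick: a difference of 4 mmHg and an SD of 10 mmHg. Its 49 per arm does not follow from a two-arm comparison with those inputs (that needs 99 per arm). This is a separate matter and is not used below.

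**Inputs.**
- From the Protocol: SD 10 mmHg (taken as the SD of single values; the Protocol does not say whether it refers to values or change), two moments, two arms.
- Assumed: drop-out of 20% per arm (10% also shown); log-odds of drop-out 0.7 to 1 per SD of baseline pressure; correlation ρ of 0.4 to 0.7 between week 0 and week 13.

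**Step 1. Shift in baseline among completers.** Let x be standardised baseline and P(drop out | x) = 1/(1 + exp(−(c + s·x))), with c set to give the chosen rate. Numerical integration over a standard normal x gives the mean of x among completers:

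| Drop-out | s = 0.7 | s = 1 |
|---|---|---|
| 10% | −0.067 | −0.091 |
| 20% | −0.130 | −0.173 |

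**Step 2. Bias with an independence fit.** Each arm's week-13 mean is off by SD × ρ × shift. The contrast is off by the difference between arms.
- Dependence in one arm only, 20% drop-out: from 10 × 0.4 × 0.130 = 0.52 to 10 × 0.7 × 0.173 = 1.21 mmHg, or 13 to 30% of 4 mmHg.
- The same at 10% drop-out: from 10 × 0.4 × 0.067 = 0.27 to 10 × 0.7 × 0.091 = 0.64 mmHg.
- Same slope (0.7) in both arms but rates of 10% and 20%: 10 × ρ × (0.130 − 0.067) = 0.25 to 0.44 mmHg.
- Same slope and rate in both arms: the shifts cancel and the bias is 0.
- Opposite slopes in the two arms, 20%: twice the one-arm figures, 1.0 to 2.4 mmHg.

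**Step 3. Bias with an exchangeable fit.** The week-13 mean is now corrected by α × (baseline mean of all − baseline mean of completers), where α is the estimated working correlation. What remains is SD × (ρ − α) × shift. Drop-out pulls α slightly below ρ. In the one-arm case at 20% the remainder is at most 0.04 mmHg; with opposite slopes it is at most about 0.2 mmHg. With two moments, exchangeable and unstructured working correlations are the same single parameter.

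**Step 4. Bias with a baseline-adjusted likelihood or ANCOVA fit.** The week-13 mean is regressed on baseline, so drop-out that depends on baseline and arm leaves a bias of about 0.

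**Step 5. Drop-out that depends on the unobserved week-13 value.** No fit in steps 2 to 4 removes this. In a large-sample simulation with 20% drop-out per arm and an odds ratio of 2 per SD in one arm only, the bias at ρ = 0.5 and 0.7 was 1.31 and 1.27 mmHg (independence) and 0.99 and 0.65 mmHg (exchangeable).

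**Step 6. Precision without drop-out.** The variance of a change contrast is proportional to 2(1 − ρ), and that of a baseline-adjusted contrast to 1 − ρ². The ratio of standard errors is √((1 + ρ)/2).
- ρ = 0.4: √0.70 = 0.837, a reduction of 16%.
- ρ = 0.7: √0.85 = 0.922, a reduction of 8%.

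This gain comes from the common baseline mean or the ANCOVA term. Changing only the working correlation of the GEE does not bring it, because with complete data the group-by-moment estimate is the same under either structure.

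**The case against.** The strongest reply is that the working correlation and the handling of missing week-13 values are usually left to a statistical analysis plan, which is not shown. The Protocol does not fix an independence structure, and an exchangeable one would nearly remove the bias from baseline-related drop-out. The intention-to-treat sentence only defines the analysis set and is correct as such. Missed training is also not a missed assessment: someone who stops training may still attend week 13. All of this stands, and the unnamed working correlation is not in itself a fault of the Protocol.

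What remains is that the Protocol does choose the model, and a group-by-moment GEE does not use baseline as a covariate. The precision loss in step 6 does not depend on any drop-out assumption or on the working correlation.

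A reader might go further and infer two things that the documents do not support:
- **That the analysis is valid only if data are missing completely at random.** Steps 2 and 3 show otherwise. The contrast is unbiased if both arms share the same rate and mechanism, and nearly unbiased with an exchangeable fit when drop-out depends on baseline.
- **That the bias can reach half of the 4 mmHg difference.** That size needs drop-out to depend on baseline in opposite directions in the two arms, or stronger assumptions still. A heavier schedule in one arm may suggest a different rate, or dependence in that arm; it gives no reason for opposite signs. Nor is half a ceiling, since extreme assumptions exceed it.

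**Conclusion.** The point holds as a worthwhile improvement to the stated method, not as a demonstrated error. Consistency of the unweighted two-moment GEE under drop-out is guaranteed in general only if drop-out is completely at random or depends on model covariates alone, and its contrast is not adjusted for baseline pressure.

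With 20% drop-out and dependence on baseline in one arm only, an independence fit would be biased by about 0.5 to 1.2 mmHg. The drop-out rate, mechanism and correlation are all assumptions, because the Protocol gives none of them. The true bias could be zero or larger. The firmer part is the 8 to 16% reduction in standard error from baseline adjustment, which rests only on an assumed correlation of 0.7 to 0.4.

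**What to change.** In the Statistical analysis section, for the continuous outcomes, replace the GEE by one of:
- a linear mixed model fitted by REML, with unstructured covariance over the two moments and a common baseline mean for the arms; or
- ANCOVA of the week-13 value on baseline, with multiple imputation of missing week-13 values that includes baseline.

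If GEE is kept, specify an exchangeable or unstructured working correlation rather than independence. This nearly removes the bias from baseline-related drop-out but does not bring the precision gain.

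Optionally, add a sensitivity analysis that shifts the imputed values of participants who dropped out, since none of these models deals with drop-out that depends on the unobserved week-13 value.

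The cost is a few sentences and slightly more analysis work. No further participants or measurements are needed, because baseline is already collected.

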# SCHEDULE

|  | 2019/2 | 2020/1 | 2020/2 | 2021/1 |
| --- | --- | --- | --- | --- |
| Submission of the project to research ethics committee | x |  |  |  |
| Training of researchers | x |  |  |  |
| Recruitment of participants | x | x | x |  |
| Evaluations and interventions | x | x | x | X |
| Analysis and discussion of results |  |  |  | X |
| Writing and submission of scientific article |  |  |  | X |

# FUNDING

Permanent materials such as blood pressure monitors, equipments for exercise sessions, as well as other permanent materials needed for project evaluations are now available at the Exercise Physiopathology Laboratory of Hospital de Clínicas de Porto Alegre and at the center of the PREVER study.

|  | Quantity | Unitary value | Total value |
| --- | --- | --- | --- |
| A4 paper (package) | 5 | R$ 13,00 | R$ 65,00 |
| Ultrasound gel (300g) | 10 | R$3,24 | R$ 32,40 |
| ECG electrode | 1000 | R$ 0,63 | R$ 360,00 |
| Rest electrocardiogram | 98 | R$ 5,15 | R$ 504,70 |
| Glycosylated hemoglobina (blood sample) | 196 | R$ 10,17 | R$ 1993,32 |
| Total cholesterol (blood sample) | 196 | R$ 1,85 | R$ 362,60 |
| Ergospirometry | 98 | R$ 30,00 | R$ 2940,00 |
| **TOTAL** |  |  | **R$ 6.258,02** |

